## 9.3 Statistical Analysis

The statistical analysis will be specified in a Statistical Analysis Plan prior to Database lock. All data analysis will be based on statistical hypothesis testing. Population variables, adverse events and efficacy variables will be formally evaluated. The primary objective of the trial is to evaluate the safety and efficacy of Anakinra treatment for episodes of acute cystitis in patients with recurrent disease. No formal sample size calculation evaluating the power of the trial has been performed. However, a consideration regarding the sample size was made based on previous studies of Anakinra in a murine acute cystitis model. For efficacy, the sample size was based on analysis of symptom scores, inflammatory parameters and bacterial cultures. A sample size of 20 patients in the Anakinra treatment group and ten in the group receiving antibiotics was deemed suitable to achieve criterion for significance (alpha) 0.05 and power 90% using the paired samples 1-tailed t-test. The null hypothesis is H0: mean change in symptom score = 0 and the alternative hypothesis is HA: mean change in symptom score > 0.

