### 3.1 Objectives

#### 3.1.1 Primary Efficacy Objective

To investigate treatment efficacy of Kineret compared to Nitrofurantoin in female patients with an acute episode of recurrent cystitis.

- a) To investigate whether Kineret is effective in treatment of acute cystitis.
- b) To investigate whether Kineret treatment decreases the incidence of recurrent cystitis.

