### 3.2 Endpoints

#### 3.2.1 Primary Efficacy Endpoint

Reduction in symptom score measured by the ACSS in the first 5 days (ACSS dynamics).

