### 4.3 Subject identification and randomisation of treatment

All enrolled subjects will be randomized 2:1 to two study treatment groups at Visit 1.

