### 9.3.2 General Principles

Non-parametric and parametric methods will be used according to the properties of the data set. All confidence intervals will be presented with 95% degree of confidence.

An observed cases approach will be used for tabulations of data by visit (i.e. involving only those subjects who attended each specific visit).

The end of treatment values will be presented for laboratory parameters (primary and secondary endpoints) and for efficacy data.

For tabulations on changes from baseline, baseline will be defined as the last assessment performed before application of Kineret.

Categorical data will be summarised using the number and percentage of subjects in each category. Continuous data will be summarised using the mean, 95% confidence interval for mean (CI), standard deviation (SD), median, minimum and maximum values.

Any changes from the statistical analysis planned in this clinical trial protocol will be described and justified in a protocol amendment and/or in the clinical trial report dependent on the type of deviation.

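### The primary objective compares Kineret with Nitrofurantoin, but the only efficacy hypothesis the protocol states is a within-arm test of change against zero

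*Protocol*

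**What the plan says.** Section 3.1.1 gives the primary objective as "To investigate treatment efficacy of Kineret compared to Nitrofurantoin in female patients with an acute episode of recurrent cystitis". The opening of section 3 likewise announces a randomised comparison with the antibiotic, and section 4.3 says "All enrolled subjects will be randomized 2:1 to two study treatment groups at Visit 1". The primary endpoint in section 3.2.1 is "Reduction in symptom score measured by the ACSS in the first 5 days (ACSS dynamics").

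Section 9.3 leaves the detailed analysis to a statistical analysis plan. It then restates the objective without the comparator ("The primary objective of the trial is to evaluate the safety and efficacy of Anakinra treatment for episodes of acute cystitis") and sizes the trial at 20 Kineret and 10 Nitrofurantoin patients, numbers that it calls "deemed suitable to achieve criterion for significance (alpha) 0.05 and power 90% using the paired samples 1-tailed t-test". It closes with the hypotheses: "The null hypothesis is H0: mean change in symptom score = 0 and the alternative hypothesis is HA: mean change in symptom score" greater than zero. Sections 9.1 and 9.3 both say that no formal power calculation was done. The rest of section 9 speaks only in general terms of parametric and non-parametric methods, and it defines baseline by reference to the application of Kineret alone.

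**The concern.** A paired t-test on change uses one arm at a time. It has no treatment term, so it cannot answer a question about Kineret compared with Nitrofurantoin. The null hypothesis of zero mean change is also weak in this setting, for three reasons:

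- Section 5.2 admits patients only with an ACSS typical-domain sum of at least 6 and symptoms that began within 6 days. They are selected on the score that is then analysed, so regression to the mean is built in.
- Acute symptoms may ease without an effective drug. The only statement on natural course is from mice (section 2.3, a self-limiting form).
- Under section 6.2 (Early Termination Visit), patients with treatment failure receive other antibiotics and stay in the study. If that happens before Day 5, the resulting fall counts in the Kineret arm.

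The risk is that a within-arm p-value is reported as evidence of efficacy from a randomised trial while the stated objective remains unanswered.

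**Working it through.** **Inputs from the protocol.** One-tailed alpha 0.05, power 90%, paired t-test, 20 and 10 patients (section 9.3). The typical domain has six items scored 0 to 3, so its range is 0 to 18 (section 22.3). No effect size, SD of change or untreated human change is given; the stated basis is a murine model.

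**Step 1. The plan's own figure.** Power is P(T > t(0.95; n−1)), where T is noncentral t with n−1 degrees of freedom and noncentrality dz × √n, and dz is mean change divided by SD of change. With neither mean nor SD stated, the 90% cannot be reproduced, only solved backwards:

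- n = 20: critical t is 1.729, and 90% power needs dz = 0.68.
- n = 10: 90% power needs dz = 1.00. At dz = 0.68 the power is about 0.63.

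A single assumed effect therefore cannot give 90% in both arms.

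**Step 2. What the stated test does with an inert drug.** Assume a mean untreated fall m and an SD of change s, so dz = m/s. For m = 3 and s = 4, dz = 0.75, noncentrality is 0.75 × √20 = 3.35, and the rejection probability is 0.94. Over the assumed range, with n = 20:

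| Untreated fall (points) | SD 3 | SD 4 | SD 5 |
|---|---|---|---|
| 1 | 0.42 | 0.29 | 0.22 |
| 2 | 0.89 | 0.70 | 0.53 |
| 3 | 0.996 | 0.94 | 0.83 |
| 4 | >0.99 | 0.996 | 0.96 |
| 5 | >0.99 | >0.99 | 0.996 |

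An untreated fall of 0.68 SD (0.68 × 3 = 2.0 points to 0.68 × 5 = 3.4 points) already gives a 90% chance of rejection. The Nitrofurantoin data do not enter the calculation. If Kineret patients fall 3 points with SD 4, the Kineret test rejects with probability 0.94 however much more the control arm improves.

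**Step 3. What 20 against 10 can support as a comparison.** For a two-sided 0.05 two-sample t-test, degrees of freedom are 28 and noncentrality is d / √(1/20 + 1/10) = d / 0.387:

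- 90% power needs d = 1.30 SD: 3.9, 5.2 or 6.5 points for SD 3, 4 or 5.
- At d = 0.68 SD, power is 0.40.
- The half-width of the 95% interval is 2.048 × SD × 0.387: 2.4, 3.2 or 4.0 points for SD 3, 4 or 5.

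Baseline adjustment can tighten these figures, but the documents give no correlation from which to say by how much.

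**The case against.** The protocol leaves the analysis to a plan that is not available, names the paired test inside a sample-size consideration, and describes itself as a pilot seeking first signs of efficacy (sections 2.4.1 and 9.1). That limits the point but does not remove it. The two hypotheses are stated without restriction, no others appear, and they do not match section 3.1.1. This is a hypothesis wrongly fixed, not detail left for later.

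A reader might infer several stronger things that the documents do not support:

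- *The comparison will never be tested and randomisation goes unused.* The unseen plan may contain a between-arm analysis, and section 3 says that a comparison will be made.
- *The false-positive rate is 83 to 100% instead of 5%.* That range holds only for assumed falls of 3 points or more. If scores truly fall, zero mean change is false and rejecting it is correct. Type I error is not inflated; the hypothesis asks the wrong question.
- *The alternative tests for worsening.* Section 9.3.2 defines baseline but no direction of subtraction, and the endpoint is worded as a reduction. The sign is undefined, no more.
- *A one-tailed 0.05 test contradicts the 95% intervals.* "All confidence intervals will be presented with 95% degree of confidence" is a general reporting rule, and section 9.3.2 lists the interval for the mean among its descriptive summaries. It is not made a decision rule.

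**Conclusion.** The point holds as a mismatch between section 3.1.1 and section 9.3, and it should be corrected before analysis. As the protocol stands, meeting its stated hypothesis would not show that Kineret works, or how it compares with Nitrofurantoin. The stated test could be met by natural recovery or regression to the mean, with probability 0.22 to about 1.00 for assumed untreated falls of 1 to 5 points and SD of change 3 to 5, and at least 0.83 once the fall is 3 points or more. These figures rest on assumptions, since the documents give no untreated human course. That the test is within-arm needs no assumption.

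Two smaller defects go with it. The sign of change in the alternative hypothesis is not defined. The bracketed term ACSS dynamics in section 3.2.1 can be confused with the Dynamik item of ACSS Part B (section 22.3), a 0 to 4 rating of change that has no baseline value and cannot be paired.

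**What to change.** In section 9.3:

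- Replace the hypothesis with a between-arm one. The primary estimate is the Kineret minus Nitrofurantoin difference in Day 5 ACSS typical-domain sum score, by ANCOVA with the Visit 1 typical score as covariate, in all randomised patients, with a two-sided 95% confidence interval. Say how Day 5 scores recorded after antibiotics for treatment failure enter the analysis.
- Report within-arm changes descriptively only.
- Withdraw or restate the 90% power statement and present the comparison as exploratory estimation, giving the detectable difference of about 1.30 SD.
- State that there is no non-inferiority margin and that a non-significant difference will not be read as equivalence.
- Define the sign of change, and say in section 3.2.1 that ACSS dynamics does not mean the Part B item.

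No new data are needed: sections 6.1 and 6.2 already schedule the ACSS at Visit 1 and Day 5 in both arms. The work is an amendment and matching text in the statistical analysis plan. The price is a less favourable stated inference and the loss of the power claim. Keeping 90% two-sided power at 0.68 SD would take about 70 + 35 = 105 patients instead of 30.

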### 9.3.1 Clinical Laboratory Evaluation

For biochemistry and haematology parameters, the absolute value and the change from baseline to Visit 6 and baseline to Visit 7 will be summarised. In addition, the laboratory parameters will be classified as 'low', 'normal' or 'high', depending on whether the value is below, within or above the reference range, respectively. Shift tables will be produced showing the categories at baseline against those at Visit 6 and baseline to Visit 7.

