#### 3.2.2 Safety Endpoints

Change in laboratory safety variables, vital signs, physical examination from baseline and the incidence of adverse events, treatment emergent adverse events, serious adverse events during the trial.

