#### Visits 2 and 5 Treatment Visits

Applicable to study patients of both treatment arms.

- Concomitant Medication
- Dispensing of Kineret®
- Adverse Events
- Vital Signs
- Blood sample (haematology and biochemistry)
- Urine analysis (RNA)
- Proteomics
- Urine analysis dip slide and bacterial culture
- Blood sample (RNA)
- Flow Cytometry urine sample
- ACSS (only on visit 5)

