#### Visit 6 (1st Follow-up visit)

Applicable to all study patients. 15 days (+/-2 days) after the last IMP administration, a follow-up visit will take place. Investigator will assess occurrence of any on-going or new AEs. AEs will be followed until final outcome as described in Section 7.4.

- Concomitant Medication
- Adverse Events
- Vital Signs
- Blood sample for assessment WBC and differential for monitoring of neutrophils granulocytes
- Urine analysis RNA
- Proteomics
- Urine analysis dip slide and bacterial culture
- Blood sample (RNA)
- Flow Cytometry urine sample
- ACSS

Safety telephone call at day 30

Applicable to all study patients.

- Concomitant Medication
- Adverse Events
- ACSS

Visit 7 (Final Visit)

Applicable to all study patients in week 26 (+/5 days). In addition patient premature withdrawn from the study will, if possible and if patient agrees, have the procedures and assessments performed according to this final visit.

- Urine pregnancy test
- Concomitant Medication
- Physical Examination
- Adverse Events
- Vital Signs
- Blood Samples for assessment WBC and differential for monitoring of neutrophils granulocytes
- Urine analysis RNA
- Proteomics

- Urine analysis dip slide and bacterial culture
- Blood sample (RNA)
- Flow Cytometry urine sample
- ACSS

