## 6.10 Laboratory Assessments

### 6.10.1 Safety Blood Tests (hematology, biochemistry)

Samples for analysis of parameters must be taken according to the schedule of trial procedures (section 6.1) or on withdrawal from or early completion of the treatment phase of the clinical trial.

| The following analyses will be performed on the venipunctured blood samples: | Parameter                                                                                                                                                                 |
|------------------------------------------------------------------------------|---------------------------------------------------------------------------------------------------------------------------------------------------------------------------|
| Haematology                                                                  | Haemoglobin
Haematocrit
Red blood cell (RBC) count
Mean corpuscular volume (MCV)
White blood cell (WBC) count, including differential count
Platelet count |
| Biochemistry (serum/plasma)                                                  | Urea
Creatinine
Sodium
Potassium
Glucose                                                                                                                      |

If any laboratory results are abnormal, the investigator should follow-up the subject as clinically appropriate.

Routine analyses of blood samples (clinical chemistry) will be processed at the central laboratory of the university hospital Giessen-Marburg, location Giessen. At the end of the clinical trial, parts of the samples are shipped to the local laboratory at the Lund University, Sweden. Handling and shipment instructions are provided in laboratory manuals by the laboratory at the Lund University.

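### Section 9.3.1 places the laboratory change and shift tables at Visits 6 and 7, where 10 of the 11 listed parameter lines are not sampled, and states none for the full panels at Visits 2 and 5

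*Protocol*

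**What the plan says.** Section 3.2.2 of the Protocol makes "Change in laboratory safety variables, vital signs, physical examination from baseline" part of the safety endpoints. Section 9.3.1 says how the laboratory part is to be tabulated. For biochemistry and haematology, "the absolute value and the change from baseline to Visit 6 and baseline to Visit 7 will be summarised". Each value is also classed as low, normal or high against the reference range, and "Shift tables will be produced showing the categories at baseline against those at Visit 6 and baseline to Visit 7". No other visit is named.

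Section 6.10.1 lists what is measured. Haematology comprises haemoglobin, haematocrit, red cell count, MCV, and then "White blood cell (WBC) count, including differential count Platelet count". Biochemistry comprises "Urea Creatinine Sodium Potassium Glucose".

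The sampling schedule differs from the analysis visits. For Visits 2 and 5, which apply to both arms, section 6.2 lists "Blood sample (haematology and biochemistry". For Visit 6 it lists only "Blood sample for assessment WBC and differential for monitoring of neutrophils granulocytes", and Visit 7 has the equivalent entry. The chart in 6.1 agrees: biochemistry is blank at Visits 6 and 7, and haematology there is restricted to white cells and differential.

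Section 9.3.2 adds that end-of-treatment values will be presented for laboratory parameters, followed by a parenthesis that refers to primary and secondary endpoints.

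**The concern.** The analysis section and the sampling schedule do not fit together. The tables are set at visits where most of the parameters are never drawn, while the visits with the complete panel have no stated change or shift table. Followed literally, 9.3.1 gives laboratory safety tables that are almost entirely blank.

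Platelets show the effect. The Kineret adverse reaction table in section 8.2.2 lists both neutropenia and thrombocytopenia at a frequency of at least 1/100. Neutrophils are within the differential and can be tabulated at Visits 6 and 7. Scheduled platelet counts exist only at Visits 1, 2 and 5, so the planned tables would hold no post-baseline platelet value. The same is true of creatinine and the other four biochemistry items.

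This is not a detail left for the analysis plan to settle. The Protocol names the visits, and the names conflict with its own schedule.

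**Working it through.** The Protocol gives no figure to reproduce; the check is a count of listed parameters against scheduled samples.

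**Inputs**
- Parameter lines, section 6.10.1: 6 haematology (haemoglobin, haematocrit, red cells, MCV, white cells with differential, platelets) and 5 biochemistry. Total 6 + 5 = 11.
- Analysis visits, section 9.3.1: Visits 6 and 7, for both the change summaries and the shift tables.
- Sampling, chart in 6.1 and lists in 6.2, which agree with each other.

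| Visit | Arms | Haematology lines (of 6) | Biochemistry lines (of 5) | Change or shift table in 9.3.1 |
|---|---|---|---|---|
| 1 (baseline) | both | 6 | 5 | reference |
| 2 | both | 6 | 5 | none stated |
| 3 | Kineret only | 1 (white cells with differential) | 0 | none stated |
| 4 | Kineret only | 0 | 0 | none stated |
| 5 | both | 6 | 5 | none stated |
| 6 | both | 1 (white cells with differential) | 0 | planned |
| 7 | both | 1 (white cells with differential) | 0 | planned |

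**Coverage as planned**
- Lines with data at Visits 6 and 7: 1 of 6 haematology and 0 of 5 biochemistry, so 1 of 11. Lines without data: 11 − 1 = 10.
- Parameter-by-visit cells: 11 × 2 = 22. Cells that can be filled: 1 × 2 = 2. Empty cells: 22 − 2 = 20.
- Sensitivity to counting: if the differential is a separate line, the total is 12, the number measured is 2 and the number missing is 12 − 2 = 10. That gives 10 of 12 and the same conclusion.

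**Coverage if the tables follow the samples**
- Visits 2 and 5: 11 × 2 = 22 cells, all with scheduled data in both arms.
- White cells with differential at Visit 3 (Kineret arm) and at Visits 6 and 7: 1 + 2 = 3 further cells, all with scheduled data.
- Total: 22 + 3 = 25 cells, none empty by design.

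**The case against.** The strongest reply is that little is lost. Four points support it.

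- The endpoint in 3.2.2 covers change from baseline during the trial and names no visit. A reader might infer from 9.3.1 that the endpoint cannot be produced. The documents do not support that: full panels at Visits 1, 2 and 5 in both arms supply it. This part of the reply stands.
- A reader might also infer that laboratory changes during dosing would go unreported. That goes too far. Section 9.3.2 promises end-of-treatment values, and for a five-day course Visit 5 is the natural reading. Section 6.10.1 asks for follow-up of abnormal results, and Appendix 1 requires any laboratory abnormality judged clinically significant to be recorded as an adverse event. These routes cover part of the ground. They do not replace the tables: a value is neither a change nor a shift, Visit 2 is not covered, the parenthesis in 9.3.2 leaves it unclear whether safety laboratory data are meant, and adverse event capture rests on the investigator's judgement.
- It is tempting to argue that the visits are wrong because Kineret, with its stated half-life of 4 to 6 hours, has been cleared by Visit 6. That is not needed and does not show a fault. The half-life concerns one arm only, and a late look for persisting or delayed change in white cells is legitimate. The fault is that the other parameters are not measured at those visits.
- An analysis plan is due before database lock and could correct the visits. It could, but 9.3.2 requires changes from the planned analysis to be described and justified in an amendment and/or the trial report, so the correction should be explicit.

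Unscheduled visits include full panels, and 6.10.1 asks for samples on withdrawal or early completion of treatment. These may add values for some patients, but they are not scheduled Visit 6 or Visit 7 data and would not fill the tables.

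**Conclusion.** The point holds as an internal inconsistency. Sections 6.1 and 6.2 agree on the sampling; 9.3.1 does not match them. At both visits named for change and shift tables, 10 of the 11 parameter lines have no scheduled data, and the complete panels at Visits 2 and 5 have no stated change or shift analysis. The laboratory safety endpoint survives; the tables meant to deliver it do not, apart from white cells and differential.

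This should be fixed, but it does not threaten the trial. No data are lost, and neither the primary endpoint nor any efficacy comparison is touched. It affects descriptive safety tables in a trial of 30 patients and can be put right at any time before database lock.

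The conclusion assumes that the chart and visit lists describe the intended sampling, that the differential is counted with the white cell line as 6.10.1 lists it, and that the Visit 1 sample serves as baseline.

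**What to change.** Rewrite section 9.3.1 so that the analysis visits follow sections 6.1 and 6.2:

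- Visits 2 and 5: absolute value, change from baseline and shift table for all haematology and biochemistry parameters, by arm.
- Visit 3: the same for white cells and differential, in the Kineret arm only and labelled so, because the control arm has no sample then.
- Visits 6 and 7: the same, limited to white cells and differential.

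In section 9.3.2, state whether the end-of-treatment presentation includes the safety laboratory parameters and, if so, that it refers to Visit 5. A table of each patient's worst post-baseline category would be a useful option, but the inconsistency can be resolved without it.

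The cost is wording and table shells, recorded as a change to the planned analysis in the way 9.3.2 requires. No new samples or visits are needed.

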### 9.3.2 General Principles

Non-parametric and parametric methods will be used according to the properties of the data set. All confidence intervals will be presented with 95% degree of confidence.

An observed cases approach will be used for tabulations of data by visit (i.e. involving only those subjects who attended each specific visit).

The end of treatment values will be presented for laboratory parameters (primary and secondary endpoints) and for efficacy data.

For tabulations on changes from baseline, baseline will be defined as the last assessment performed before application of Kineret.

Categorical data will be summarised using the number and percentage of subjects in each category. Continuous data will be summarised using the mean, 95% confidence interval for mean (CI), standard deviation (SD), median, minimum and maximum values.

Any changes from the statistical analysis planned in this clinical trial protocol will be described and justified in a protocol amendment and/or in the clinical trial report dependent on the type of deviation.

